### Safety and adverse events

Two safety and tolerability outcomes are defined in the protocol: the occurrence of intussusception within the first 28 days after randomisation and the occurrence of serious adverse events between randomisation and 36 months. The occurrence of intussusception will be reported in terms of frequency and proportion, by treatment arm and overall. The serious adverse events as defined by [25] will be reported as frequency and proportion, stratified by treatment arm and overall. While no analysis will be performed on the safety and adverse event data, they will be included in the competing risk sensitivity analysis mentioned earlier.

### Pre-specified subgroup analyses

No subgroup analyses were pre-specified in the protocol.

### Sensitivity analyses

As a sensitivity analysis, we will examine the results at the final analysis for the clinical endpoint by fitting a piecewise exponential model that permits the baseline hazard to be a function of treatment, i.e. treatment level time varying hazards [43].

Given that the endpoints are binary and event times (with possible right censoring), there will be no data outliers.

## Data monitoring

The processes around trial monitoring, including data monitoring, are defined in the quality assurance procedures of the ORVAC protocol document.

In brief, data will be sourced from a specifically designed clinical record form (CRF) comprising consent forms, eligibility assessment, visit record, adverse event details and protocol deviations. Data is entered from these sources into a trial database by study personnel. Data queries are raised by the data manager and cleaned by both the data manager and trial statistician. All planned final analyses identified herein are to be performed after the study is completed and the database has been cleaned and locked. However, the interim analyses will be performed on incomplete data in that amendments may occur to the data that was used in an interim at some time after the interim analysis is completed. Our assumption here is that less than 5% of the sample size at any given interim analysis will be subsequently amended.

## Missing data

Within Bayesian analyses, missingness is either ignorable or non-ignorable. In the former case, the parameters relating to the measurement are distinct from those that relate to missingness and the mechanisms are termed either Missing Completely at Random (MCAR) or Missing at Random (MAR). For MCAR, a complete-case analysis will result in reduced efficiency but is unbiased. However, for MAR, a complete-case analysis will be both inefficient and biased. Non-ignorable missingness relates to those data that are Missing Not At Random (MNAR). Under MNAR, an extra model is required to predict the missingness.

One of the advantages of using Bayesian methods is that they offer a natural way to simultaneously impute missing values and fit models on the observed and imputed data [44]. After exploring the amount and patterns of missing data and the association with other variables, we will impute as necessary using a fully Bayesian approach following methods as per [44].

## Evaluation of operating characteristics

Except for the simplest of cases, the operating characteristics for a Bayesian adaptive trial are analytically intractable. Therefore, these are usually estimated by Monte Carlo methods, which are a general purpose tool for optimisation and integration problems [45]. In the context of exploring the operating characteristics of a given trial, the idea is to formulate a data generating process (DGP) that represents expected and plausibly extreme outcomes for the actual trial. However, as is the case here, it may be necessary to simplify the data generating process and/or analysis approach in order to be able to run the simulations within a workable timeframe. Using the assumed DGP, trial data can be simulated many times and the resulting ‘virtual trials’ are analysed using methods described shortly. Various characteristics of the DGP can then be derived. For example, the expected type I error (false positive rate) is derived from data that are generated under a null effect configuration and estimated from the proportion of times that we falsely detect a difference between the treatment arms in the final analysis.

We have examined the operating characteristics of the ORVAC trial in more than 300 scenarios using Monte Carlo simulation of the parameter space associated with a representative data generating, sampling and modelling process. For the immunological endpoint, seroconversion was modelled via a series of independent Bernoulli trials with control arm probabilities of seroconversion (the baseline seroconversion rate) between 0.1 and 0.7 and a change of probability of seroconversion in the treatment arm between 0 (the null case) and 0.15 above the baseline rate. Additionally, we modelled information delays associated with processing the immunological endpoint of 0.5 and 0.7 months. For the clinical endpoint, we modelled time to event as an exponentially distributed random variable. The control arm median time to event was set at 20–50 months and a change in the median time to event varied between 0 (the null case) and 15 months. Event times were censored at 36 months of age. We modelled accrual using a Poisson process generating approximately 30 and 50 participants per quarter. Age at vaccination was modelled using a uniform distribution with lower and upper bounds of 6 and 12 months respectively. The co-primary endpoints were modelled as independent random variables.

## Probability thresholds for interim and final decisions

Table 2, presented earlier, details the thresholds that were identified through simulation to be used for the interim and final analysis.

## Type I error rate

Table 3 provides examples of the type I error rates obtained over a range of plausible scenarios. In all cases, the type I error/false positive rate is controlled at the *α*<0.05 level for both co-primary endpoints. Adjustment for multiple comparisons is addressed via the probability thresholds that are selected to be used in the analyses.

**Table 3 Tab3:** Type I error rates for null configurations

Parameters		Accrual per 3 months	Info. delay	Samp. size mean (SD)	Type I error rate	
Median time to event	Prob. Seroconv.				Clinical	Immuno
50	0.7	50	0.7	259 (259.2)	0.036	0.032
50	0.7	30	0.7	247 (238.4)	0.041	0.028
50	0.7	50	0.5	264 (266.3)	0.039	0.030
50	0.7	30	0.5	252 (244.8)	0.043	0.032
50	0.4	50	0.7	261 (262.2)	0.033	0.031
50	0.4	30	0.7	247 (238.6)	0.042	0.029
50	0.4	50	0.5	259 (260.4)	0.037	0.028
50	0.4	30	0.5	248 (242.2)	0.042	0.032
50	0.1	50	0.7	256 (254.9)	0.031	0.031
50	0.1	30	0.7	247 (237.7)	0.038	0.032
50	0.1	50	0.5	259 (259.0)	0.036	0.031
50	0.1	30	0.5	246 (239.2)	0.040	0.032
35	0.7	50	0.7	253 (253.5)	0.034	0.030
35	0.7	30	0.7	245 (236.8)	0.039	0.029
35	0.7	50	0.5	260 (259.0)	0.040	0.030
35	0.7	30	0.5	247 (239.6)	0.043	0.034
35	0.4	50	0.7	264 (263.3)	0.039	0.031
35	0.4	30	0.7	246 (237.6)	0.043	0.031
35	0.4	50	0.5	262 (262.8)	0.038	0.030
35	0.4	30	0.5	247 (237.9)	0.042	0.030
35	0.1	50	0.7	259 (256.7)	0.033	0.031
35	0.1	30	0.7	246 (238.4)	0.035	0.035
35	0.1	50	0.5	259 (258.9)	0.036	0.028
35	0.1	30	0.5	242 (231.9)	0.038	0.030
20	0.7	50	0.7	264 (261.5)	0.037	0.028
20	0.7	30	0.7	244 (233.4)	0.038	0.027
20	0.7	50	0.5	260 (259.1)	0.041	0.029
20	0.7	30	0.5	247 (235.8)	0.043	0.027
20	0.4	50	0.7	258 (256.9)	0.036	0.030
20	0.4	30	0.7	246 (236.9)	0.041	0.029
20	0.4	50	0.5	262 (263.4)	0.040	0.029
20	0.4	30	0.5	248 (237.6)	0.044	0.030
20	0.1	50	0.7	257 (250.7)	0.034	0.031
20	0.1	30	0.7	244 (233.6)	0.035	0.029
20	0.1	50	0.5	256 (254.4)	0.036	0.033
20	0.1	30	0.5	242 (231.1)	0.038	0.032

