We will calculate the probability that the log odds ratio (*β*_trt_) is greater than zero. If this probability exceeds 0.97, chosen by simulation to control the type I error, we will conclude a successful treatment effect of increased probability of seroconversion in the treatment arm. In notation, we conclude a treatment effect has been demonstrated if $\mathbb {P}(\beta _{\text {trt}} > 0)> 0.97$. We will report both absolute values of the proportion of participants that seroconverted in each arm and the treatment effect size as a difference in proportions and as odds ratios.

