For the shape parameter, *a*, we will adopt an exponential distribution prior with rate 0.7. This is consistent with values less than 10 and supports increasing and decreasing hazards with approximately equal probability. For the parameters in the linear predictor (the scale parameter and the hazard ratios), we will adopt independent normal priors (mean zero and standard deviation of 10). The normal priors are consistent with values on the log scale between − 15 and 15.

We will report the median time to event in each group and hazard ratios to quantify the treatment effect. In an analogous approach to that used in the immunological outcome, we will compute the probability that the parameter estimate for the treatment term is less than 0. If this probability exceeds 0.97 in the covariate-adjusted model, then we will conclude that a third scheduled Rotarix dose results in a treatment effect corresponding to a lower hazard of medical attendance in the treatment arm. In notation, we will conclude a treatment effect if $\mathbb {P}(\theta _{trt} < 0)> 0.97$.

We will use the methods as described above in the interim analyses including a single covariate for the treatment effect and using the predictive probability thresholds summarised in Table 2 for decision-making.

**Table 2 Tab2:** Probability thresholds for evaluating statistical triggers at interim and final analyses

Posterior/predictive	Decision	Threshold	Comment
Posterior	Win	0.97	Probability threshold to test that treatment difference is greater than zero
Predictive	Expected success	0.90	Proportion of successful trials must be greater than this threshold to claim expected success
Predictive	Futility	0.05	Proportion of successful trials must be in less than this threshold to claim futility
Predictive	Stop venous sampling	0.90	Proportion of successful trials must be greater than this threshold to stop venous sampling

In the final analyses for the clinical endpoint, if $\mathbb {P}(\theta _{trt} < 0) > 0.97$ in the adjusted model, we will claim trial success.

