### Interim analyses of co-primary outcomes

Bayesian adaptive trials rely on accumulating data and pre-specified decision rules to trigger adaptations. However, in order to ensure trial integrity, extensive simulation of the trial is required to investigate and quantify the operating characteristics such as the type I error rates, power and expected sample size under a range of hypothetical trial scenarios.

In this section, we outline the decision processes used for the interim analyses. Details on the simulations that were used to evaluate the operating characteristics of the trial are provided in a later section.

A simplified flow chart for the interim analyses and decision rules is presented in Fig. 1. The first interim analysis on the immunological endpoint will occur when 70 participants have full (baseline and follow-up) immunologic results. Further interim analyses occur after every subsequent 50 children or after every 3 months, whichever occurs sooner, unless there have been no new entrants. If there are no new blood samples and/or events, then we will defer the full analysis until the next scheduled interim. Analysis of the clinical endpoint will start when 200 children are enrolled in order that there are enough events to meaningfully undertake a time-to-event analysis.

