Next, we will test for futility by computing the predictive probability of observing a treatment effect under the assumption that we continue to the maximum sample size (*n* = 250) for the immunological endpoint. A predictive probability is computed using the following steps.
Take a draw from the joint posterior distribution.Use the draw to simulate random variables from a Bernoulli distribution to impute the immunological results that are not yet available for the enrolled participants with pending immunological results and the immunological results for future participants that are currently unenrolled up to the maximum sample size of 250.Combine the observed and the simulated data to form a complete dataset.Fit a logistic regression model to the complete dataset and compute the probability that the treatment effect is above zero.If the probability that the treatment effect is greater than zero is above a threshold value, then consider the trial successful and increment a counter of the number of successful trials.Go back to step 1, repeating the process at least 1000 times.

At the end of the process, we know the number of times that the trial was deemed successful from which we can compute the probability of predicted success (PPoS) as:
6$$\begin{array}{*{20}l} \textrm{PPoS}= \frac{1}{k} \sum_{1}^{k} \mathrm{I}[\mathbb{P}(\beta_{\text{trt}}>0)>0.97] \end{array} $$

where I() represents an indicator function evaluating to 1 if the contained expression is true and 0 otherwise, *β*_trt_ is the log odds ratio of seroconversion in the treatment arm versus the control arm and *k* is the total number of simulated datasets. If the PPoS is less than the futility threshold, then stop for futility and cease enrolment.

Next, if futility was not established, repeat the above process; however, only impute for the enrolled participants that do not yet have complete immunological data. If the resultant PPoS is greater than the threshold to stop venous sampling, we will cease venous sampling. If either the futility or stop venous sampling thresholds are triggered, we will undertake a final analysis on the immunological outcome once all the enrolled participants (at the time of the trigger) have been followed to completion.

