Assuming that the trial has not been stopped for futility, we will start analysing the clinical endpoint at the next scheduled interim analysis after 200 participants have enrolled. The interim analysis process for the clinical outcome is similar to that of the immunological outcome, but with the added complication of censoring.

First, we will compute the joint posterior distribution of the model parameters using methods detailed earlier, namely a Weibull proportional hazards model with an indicator variable for treatment status. To compute the posterior, we will use the data from all participants that have had at least one surveillance visit.

Next, we will test for futility by computing the predictive probability of observing a treatment effect under the assumption that we continue to the maximum sample size (*n* = 1000) for the clinical endpoint. A predictive probability is computed using the following steps.
Take a draw from the joint posterior distribution.Use the draw to simulate random variables from a left-truncated Weibull distribution to impute the event times for the enrolled participants that are not yet censored due to age but are yet to have an event. Additionally, use the draw to simulate the event times from a Weibull distribution for the participants not yet enrolled, up to the maximum size (*n* = 1000).If the simulated event times occur after the participant is 36 months old, then censor at 36 months less the age of enrolment, which, if unknown, is drawn from a uniform distribution between 6 and 12 months.Combine the observed and the simulated data to form a complete dataset.Fit a Weibull proportional hazards model to the complete dataset and compute the probability that the treatment effect is below zero.If the probability that the treatment effect is below zero is above a threshold value, then consider the trial successful and increment a counter of the number of successful trials.Go back to step 1, repeating the process at least 1000 times.

At the end of the process, we know the number of times that the trial was deemed successful from which we can compute the probability of predicted success (PPoS) as:
7$$\begin{array}{*{20}l} \textrm{PPoS}= \frac{1}{k} \sum_{1}^{k} \mathrm{I}[\mathbb{P}(\theta_{\text{trt}}<0)>0.97] \end{array} $$

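### Table 3's null mean sample sizes (242–264) are not reproduced by the stopping rule written in the plan, which gives about 155–195 under the plan's own simulation models

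*SAP article*

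**What the plan says.** Under Type I error rate, the article states: "Table 3 provides examples of the type I error rates obtained over a range of plausible scenarios". Each row of that table also carries a mean and SD of the total sample size under the null.

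Under Interim analyses of co-primary outcomes, the look schedule is: "The first interim analysis on the immunological endpoint will occur when 70 participants have full (baseline and follow-up) immunologic results"; then "Further interim analyses occur after every subsequent 50 children or after every 3 months, whichever occurs sooner". At each look the predictive probability of success is projected to 250 immunological results. The consequence is explicit: "If the PPoS is less than the futility threshold, then stop for futility and cease enrolment". The same consequence is written for the clinical endpoint, projected to 1000. Clinical looks come later: "Analysis of the clinical endpoint will start when 200 children are enrolled", and they are conditional: "Assuming that the trial has not been stopped for futility, we will start analysing the clinical endpoint".

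Table 2 sets futility at 0.05 ("Proportion of successful trials must be in less than this threshold to claim futility") and a win at a posterior probability of 0.97. For the immunological endpoint the text says "If this probability exceeds 0.97, chosen by simulation to control the type I error".

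Evaluation of operating characteristics describes the simulations: Poisson accrual of about 30 or 50 per quarter, result delays of 0.5 or 0.7 months, Bernoulli seroconversion, exponential event times, independent endpoints, and beta-binomial and gamma-exponential models. It discloses that these models are simpler than the MCMC models of the trial. It does not disclose a different stopping rule.

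**The concern.** With no treatment effect, a futility test that starts at 70 results and repeats every 50 children or 3 months should end most trials well before 250 infants. Table 3 nevertheless reports means near 250, with SDs about as large as the means. An SD of that size needs a substantial share of null trials to run far past 250.

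Table 3 is the only tabulated support for the claim that type I error stays below 0.05 on both co-primary endpoints. If its runs used a different rule, the operating characteristics of the rule applied at live interims have not been shown.

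**Working it through.** **Inputs.** From the article: first look at 70 results, then every 50 children or 3 months; clinical looks from 200 enrolled; futility below 0.05, win above 0.97, expected success and venous-sampling stop above 0.90; maxima 250 and 1000; 1:1 allocation; the accrual, delay and data models above. Assumed: Beta(1,1) and Gamma(1,50) priors (other gamma priors moved the mean by about 2), and all sampled infants evaluable.

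**Calibration on figures that do reproduce.** Fixed-sample power with 125 per arm and one-sided 0.03 is 0.385 (0.4 v 0.5), 0.69 (0.4 v 0.55), 0.63 (0.1 v 0.2) and 0.90 (0.1 v 0.25). The article states around 40%, around 70%, over 60% and well over 80%. The 0.97 threshold and the 250 maximum are therefore read correctly.

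**Boundary calculation.** With information fraction f = n/250 and a flat prior, the predictive probability is below 0.05 when Z < z(0.97)·√f − z(0.95)·√(1−f). At n = 70, f = 0.28: 1.881×0.529 − 1.645×0.849 = −0.40, so 34% of null trials are futile at the first look. Cumulatively the figures are 34%, 58%, 77% and 90% at 70, 120, 170 and 220 results, and 97% if 250 is also tested.

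Send every survivor to 1000, ignoring clinical stopping, with no test at 250:

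70×0.34 + 120×0.24 + 170×0.19 + 220×0.13 + 1000×0.10 = 213.5.

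With a test at 250, the last term becomes 250×0.07 + 1000×0.03 = 47.5, giving 161 (159 unrounded). With quarterly looks at 30 per quarter the two values are 203 and 152. A 0.7-month delay adds pending infants to stopped trials: 50/3×0.7 = 12 or 30/3×0.7 = 7. With 90% stopped, that gives 214 + 0.9×12 ≈ 225 and 203 + 0.9×7 ≈ 209.

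**Simulated null mean N** (several independent implementations, mostly 1,500–8,000 trials per scenario):

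| Reading | 50 per quarter | 30 per quarter |
|---|---|---|
| Table 3 | 253–264 (SD 251–266) | 242–252 (SD 231–245) |
| Written rule, futility also tested at 250 | 157–171 (SD 107–131) | 146–156 (SD 103–121) |
| Written rule, no test at 250 | 188–194 | 164–172 |
| Most favourable: no test at 250, 6-monthly surveillance, extra follow-up lag | 198–210 | 165–178 |
| Ceiling (survivors set to 1000), 0.5–0.7 month delay, no test at 250 | 210–235 | 183–214 |
| Ceiling, 2-month delay, no test at 250 | 237–255 | 196–206 |

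Together, the two written-rule rows run at about 155–195, with the lowest runs at 146. Standard errors are about 1–7. Table 3's own standard error, from 10,000 null trials, is about 259/√10,000 = 2.6.

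**What Table 3's mean and SD imply.** For N between 70 and 1000, the share of trials passing 250 is at least [SD² + mean² − 320·mean + 17,500]/697,500, where 320 = 70 + 250, 17,500 = 70×250 and 697,500 = 930×750. For 259 (259.2): (67,185 + 67,081 − 82,880 + 17,500)/697,500 = 0.099. For 242 (231.1): 0.075. That minimum is attained only if all of those trials reach 1000. Under the written rule only 0.1–1.7% of null trials reach 1000.

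**Error rates.** Under the written rule the re-simulated clinical error is about 0.02–0.03 (Table 3: 0.031–0.044) and the immunological error about 0.034–0.06 (Table 3: 0.027–0.035). The immunological figure depends on how the final analysis after a venous-sampling stop is counted, which was assumed.

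**The case against.** The strongest reply is that the article discloses a simplified simulation, representative of the planned analyses but not identical to them, and that code, figures and supplements are not shown. The disclosed simplification is conjugate models in place of MCMC. The check used those models, so that caveat does not explain the gap. It is true, however, that surveillance timing, the delay clock and the handling of the look at 250 are not described.

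A reader might go further and infer that no row of Table 3 could arise from the written rule. That is too strong. With a 2-month delay, no test at 250 and clinical stopping ignored, the 50-per-quarter ceiling reaches 255, within Monte Carlo error of the lowest rows (253 upward). At 30 per quarter, if looks came only every 50 children and the delay were 2 months, the ceiling reached 244. But the text says whichever is sooner, so that is not the written schedule.

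The evaluable fraction also matters. Seroconversion is defined among infants with baseline IgA below 20 U/ml, and the article does not say what fraction of sampled infants the simulations treated as evaluable. An illustrative 50% gave means of 261 and 241, near Table 3, but SDs of 146 and 133, far below its 231–266.

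One might also guess the cause, for example that immunological futility testing ended early and stopped only about 60% of null trials. This is conjecture: runs with about 88% stopped also came near Table 3's mean and SD at 50 per quarter.

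**Conclusion.** The discrepancy stands. Against the midpoints of the written rule without a test at 250 (191 and 168), Table 3's averages are 259.6/191 = 1.36 and 246.2/168 = 1.47 times as large. Against the most favourable as-written readings, its lowest rows are still 253/210 = 1.20 and 242/178 = 1.36 times as large. The 30-per-quarter rows are the decisive evidence: they exceed even the survivors-to-1000 ceiling by about 30 (242 − 214 = 28 at the closest).

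This rests on 1:1 allocation, all sampled infants evaluable, weakly informative priors and the look schedule as written. Which rule was actually simulated cannot be identified from the article.

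A reader might infer that type I error is not controlled. The documents do not support that: the re-simulated clinical error is below 0.05, and the immunological range straddles 0.05 only under an assumed way of counting venous-sampling stops. What can be said is that Table 3 does not show the expected sample size of the written rule, and that its error rates may belong to a different one. Nor does the article support any claim about figures given to a funder.

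**What to change.** Re-run the existing simulation code with exactly the rules under Interim analyses of co-primary outcomes and replace the sample-size, SD and both error-rate columns of Table 3. If the simulated rule is the intended one, correct the interim text to match it instead. Either way, do this before the next interim analysis.

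State with Table 3: the look schedule; whether immunological futility is tested at the completed 250; whether clinical futility was active; whether the delay runs from enrolment or from the 28–55 day sample; and the fraction of sampled infants treated as evaluable.

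The cost is one re-run of code that the article says is under version control, plus a corrected table or a few sentences of rule text. No participants or data collection are affected.
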